**Assignment of interventions: Blinding**

**Who will be blinded {17a}**

Participants and care providers will not be blinded. Researchers will not be blinded during the conduct of the study to support the smooth-running implementation of the intervention. However, data analysts will be blinded during the data analysis period.

**Data collection and management**

**Plans for assessment and collection of outcomes {18a}**

There are several methods of data collection. The socio-economic and biobehavioural surveys occur over three time periods: baseline, 6 months after baseline (midline), and 12 months after baseline (endline). The surveys are administered in both French and English, depending on the participant's language preference. The primary outcomes of the study are STI acquisition and HIV status will be measured via the biobehavioural and socioeconomic survey conducted at baseline, midline and endline. At baseline, we will test for syphilis, chlamydia, gonorrhoea and trichomoniasis. For financial reasons, we will only collect HIV and the two most prevalent STIs at the midline. At endline we will test for all the STIs tested at baseline (syphilis, chlamydia, gonorrhoea and trichomoniasis). In addition, to allow for a better understanding of the participants' non-sexually transmitted infections status, the levels of GV, Mobiluncus, Candida and streptococcal in the vagina will also be tested. Testing the levels of these bacteria and fungi is a secondary outcome. It is important as sexual activity is associated with an increased risk of imbalance of these bacteria or fungi in the vagina which may lead to infections such as Bacterial vaginosis (BV), Candidiasis and Group B Strep infection. Evidence suggests that there is a positive relationship between a person having these infections and an STI and HIV(17). Biological tests (blood tests and vaginal swabs) to test for STIs, HIV and non-sexually transmitted bacteria and fungi are conducted at the same time as the socioeconomic survey.

Other secondary outcomes are measured via the biobehavioural and socioeconomic survey conducted at baseline, midline and endline. Additional measures for secondary outcomes will also be captured in the fortnightly SMS survey. The survey questionnaire will include sociodemographic questions, income, health status, demand for healthcare, economic shocks, STI prevention, risky sexual behaviours, violence, personality traits and preferences.

The procedures for each test are as follows. For HIV, serological testing will be based on a venous blood draw and follows national procedures, including both pre-and post-test counselling. HIV testing utilised dual rapid testing (Alere Determine ^TM^ HIV – ½ and OraQuick HIV – ½ ) based on the national testing protocol (Figure 2). At midline and endline, participants with undetermined tests will be referred to the military hospital of Yaoundé for an ELISA test. Patients who test positive will be linked into care.

Figure 2: HIV testing algorithm based on Cameroon national protocol

Syphilis testing will utilize rapid VDRL and Treponema pallidum hemagglutination assays (TPHA) for the detection of syphilis antibodies and classification of primary, active and past infection (Figure 3). The testing algorithm will be based on the national protocol, but FTA-ABS is not available in Cameroon for confirmatory testing. Subsequently, we will not exclude false-positive VDRL tests which will be considered positive. For midline and endline we will only consider active cases of syphilis. Following the blood draw, participants received post-test counselling until results were available 30–40 minutes after testing. Participants who test positive will receive treatment for free. We will contact them to find out if the treatment was taken and, for those who have a partner, to understand if they provided information about their infection to their partner.

Figure 3: Syphilis testing algorithm adapted from the Cameroon national protocol

Chlamydia testing will utilize Chlamydia Rapid Test Kit on vaginal swabs and include pre-and post-test counselling. A swab specimen collected from the patient will be treated with an extraction reagent. The Chlamydia rapid test dipstick is immersed in the extraction sample. The liquid migrates through the absorbent area and along the membrane on the Chlamydia rapid test. As the mixture flows along the membrane of the Chlamydia rapid test, the complex is captured by the antibody immobilized in the test zone (T) of the membrane, producing a visible rose-pink colour band and at the same time in the control zone (C). A rose-pink line in the control zone (C) indicates the Chlamydia rapid test is working properly. When only a control line appears with no test line, the Chlamydia trachomatis antigen has not been detected and the Chlamydia rapid test result is considered negative.

Gonorrhoea testing will utilize Gonorrhoea Rapid Test Kit on vaginal swabs and include pre-and post-test counselling. A swab specimen collected from the patient will be treated with an extraction reagent. The Gonorrhoea rapid test dipstick is immersed in the extraction sample. The liquid migrates through the absorbent area and along the membrane on the Gonorrhoea rapid test. As the mixture flows along the membrane of the Gonorrhoea rapid test, the complex is captured by the antibody immobilized in the test zone (T) of the membrane, producing a visible rose-pink colour band and at the same time in the control zone (C). A rose-pink line in the control zone (C) indicates the Gonorrhoea rapid test is working properly. When only a control line appears with no test line, the Gonorrhoea trachomatis antigen has not been detected and the Gonorrhoea rapid test result is considered negative.

There is no rapid test for trichomoniasis, the testing for these STIs will be subcontracted to CRESAR (Research centre for the armed forces). CRESAR is a laboratory which has been based on the JHCP premises for over 20 years. Serum samples will be stored in a freezer (-80°C). Cervicovaginal samples are discarded immediately after testing. The collected data are stored in a register and in a computer. In electronic format, the data is stored in Excel format (without a password). The persons having access to the data are the staff and the trainees authorised by the head of CRESAR. The information stored in the register and computer is, for each participant, the identification number, age, date of collection, time of collection (only for cervicovaginal samples), date and time of receipt, name of the collection site, name of the person transporting the samples from the collection site to CRESAR, name of the person receiving the samples at CRESAR, results of the tests performed. The samples are kept for the duration of the study, at the end of the study the samples will be disposed of by incineration.

**Plans to promote participant retention and complete follow-up {18b}**

**Participant retention**

Participants are not incentivised or coerced to participate in the study. During the informed consent process, the benefits of the study are outlined in detail to encourage participant retention. The primary benefit highlighted is the possibility that this project will contribute to the proposal of public policy intervention to improve the quality of life of young women who engage in transactional and commercial sex.

In addition, all participants receive compensation for their time and travel costs. Participants are compensated 2000 FCFA (2.57 GBP, in 2022 prices) for their time and travel when responding to on-site questionnaires. This compensation will act to reduce any barriers to participant participation (e.g., transport fees). In addition, they receive free STI and HIV testing on-site at baseline, midline and endline. Those with a positive STI test will be offered free treatment (regardless of group status). This will be covered by POWER directly and not by the health insurance package for those in the treatment group. HIV-positive participants will be referred to initiate antiretroviral treatment.

Participants receive airtime to reply to weekly SMS diary surveys and an additional financial incentive. To achieve higher retention and completion rates a compensation for their time of 1000 FCA francs (1.28 GBP, in 2022 prices) is offered to all participants with a completion rate of diaries superior to 90% over the last 30 days.

To retain participants in the control group, the project offers the same health insurance product to all eligible control group participants at the end of the data collection period. To be eligible for this health insurance product, control participants must remain in the study by completing all follow-up surveys and responding to the SMS survey.

Further to the potential benefits of the study, study site staff are also responsible for supporting the development and implementation of procedures to support the retention of participants, using their knowledge of the context. Peer leaders (at HF) and mobilisers (at RENATA), CBO staff members who work closely with the target group, will use their extensive experience and networks to encourage participants to continue participation in the study. The study Advisory Group will also be consulted about the retention strategies of participants.

**Participant withdrawal**

Participation is voluntary and participants can withdraw at any time, without giving reasons, by notifying a project staff member. Participant information already collected will be suppressed from the dataset. For control participants, withdrawal from the study means that participants are no longer entitled to the health insurance product provided at the end of the study. Withdrawal of participants on the treatment arm of the study will not impact any services or medical treatment they receive or any relationships they have with those treating them outside of the POWER project. However, any treatment or services that the participant and/or their nominated economic dependents receive will no longer be covered by health insurance provided by the POWER project. If the participant chooses to withdraw, they must choose to either stop ongoing treatments for themselves and their economic dependents or find an alternative means of paying for them.

**Data management {19}**

Socioeconomic questionnaires will be administered by enumerators in the field. All potential participants will be screened before recruitment onto the study to ensure they have not already participated. Participant responses are entered directly into an ODK-based questionnaire using Android tablets and uploaded to the ODK secure server in the UK when a 3G/WIFI connection is available (immediately, or at the end of each day). On survey completion, the data will be transferred to the UCL Secure Server, a fully encrypted (SSL) server with a direct data link to the android device. The ODK-based questionnaire is programmed with a logic that minimises missing data (e.g., enumerators will not be able to skip questions) and data quality (e.g., range checks will be conducted regularly). Any issues regarding data quality will be reported to the Principal investigator (PI) and directly to the enumerators and the team in the field.

Biobehavioural survey data will be held on the laboratory registry, which is a confidential registry that does not contain any identifiable personal information. The laboratory registry is paper-based (there are no facilities to have an electronic database) and will be kept securely in a locked cabinet. Paper-based data (laboratory records) will be securely transferred to the JHCP office where they will be transferred to a centralized, 128-bit encrypted and password-protected database. All electronic and encrypted data will be transferred securely to the UCL Secure Server.

Responses, using participant telephones, to the weekly SMS sexual diaries are sent directly to the dedicated server at MTN Cameroon. This server is dedicated to this study and will only contain POWER project data. This server is fully encrypted (SSL) and complies with all international standards and norms in terms of hardware and software security (firewall, antivirus, hubs, VPN). The server is in a data centre in Yaoundé, Cameroon, which is a secure building with fire protection systems, generators, redundant air conditioning, and access security). Only the PI of the study and the director of DINA surveys will have access to the data held on the password-protected server. Data is downloaded and exported to excel weekly and stored immediately on the UCL Secure Server. The data will be deleted from the MTN Cameroon dedicated server for up to three years after data collection, or earlier if requested.

In-depth interviews and focus groups will be audio-recorded using an encrypted capture device. The recordings are anonymised and transcribed verbatim in the interviewees' language (French) and transcribed into English using Microsoft Word by an independent professional transcription company. All files will be password protected at all times. They will be transferred to the UCL Secure Serve before deleting them from the device. Subsequently, they will be imported into Nvivo for anonymisation and analysis. Only the research team will have access to the in-depth interview and focus group data.

All data will be stored in accordance with University College London's data storage policies.

After completion of the project, data will be made openly available through the UCL data repository, subject to the ability to remove personally identifiable information. Data will be deposited with UCL research data repository (<https://www.ucl.ac.uk/library/research-support/research-data-management/ucl-research-data-repository>), where it will be given a Digital Object Identifier (DOI). The DOI will be cited in project reports and journal publications through a Data Access Statement or citation list. Metadata will also be made available to 3rd party research catalogues, such as https://datamed.org/.

Anonymised data will be made openly available using a permissive licence, such as Creative Commons Attribution (CC-BY). If complete anonymity cannot be provided, it will be made available through a controlled access system. If data must be made available via controlled access, interested parties will be asked to provide information on their research (purpose, institutional affiliation, ethics approval) and sign a data sharing agreement indicating they will comply with the consent form and will not attempt to re-identify individuals. Access requests will be evaluated by the project team in the first instance. In cases where an access request is denied and the requester wishes to appeal, the request will be escalated to the UCL Research Governance Committee for consideration.

**Confidentiality {27}**

The following measures have been put in place to ensure data confidentiality and to respect the privacy of participants:

1. Implementation of and compliance with the code of ethics

All study staff, inclusive of hired and trained experienced local enumerators and interviewers, must sign a commitment to comply with the code of ethics. Research partners with access to data (JHCP and DINA surveys) have signed a sub-contract with a clause which ensures that all data collected must remain confidential.

1. Participation is confidential

Socioeconomic and biobehavioural data collection and in-depth interviews and focus groups will be conducted in a private location at the CBOs. Participants must not share a telephone to be enrolled in the SMS survey. They are required to confirm that they have their own, password-protected, telephone and can respond to SMS messages. This is to ensure that only the participant reads and responds to the SMS survey.

1. Secure storage of data

During the trial, all paper-based records will be kept securely in a locked cabinet, in a locked office, and securely transferred to the JHCP office where they will be transferred to a centralized, 128-bit encrypted and password-protected database. All electronic data will be stored on the UCL Secure Server.

1. Aggregation and anonymisation of data

Individual responses will be deidentified and aggregated for analysis and reporting. All published findings, including any quotes used, will not allow for individuals to be identified. All results will be presented in aggregate form.

**Plans for collection, laboratory evaluation and storage of biological specimens for genetic or molecular analysis in this trial/future use {33}**

Once participants have completed the ODK-based socioeconomic survey (0 months, 6 months and 12 months) they will also undergo etiological testing for STIs (chlamydia, gonorrhoea, trichomonas, syphilis) and HIV. Participants will also undergo testing for additional bateria and fungi in the vagina (GV, Mobiluncus, Candida and streptococcal) at endline. Rapid tests are conducted in the CBOs laboratory for chlamydia, gonorrhoea, syphilis and HIV. No rapid test for Trichomoniasis is available in Cameroon, therefore testing will be subcontracted to CRESAR (Centre de Recherche sur la Santé des Armées), a laboratory which has been based in the JHCP premises for over 20 years.

Serum samples will be stored in a freezer (-80°C). Cervicovaginal samples are discarded immediately after testing. The collected data are stored in a register and a computer. In electronic format, the data is stored in Excel format (without a password). The persons having access to the data are the staff and the trainees authorised by the head of CRESAR. The information stored in the register and computer is, for each participant, the identification number, age, date of collection, time of collection (only for cervicovaginal samples), date and time of receipt, name of the collection site, name of the person transporting the samples from the collection site to CRESAR, name of the person receiving the samples at CRESAR, results of the tests performed. The samples are kept for the duration of the study, at the end of the study the samples will be disposed of by incineration.

**Statistical methods**

**Statistical methods for primary and secondary outcomes {20a}**

All statistical analyses will be conducted using STATA. Descriptive statistics will first be used to summarise participant characteristics between the study groups. To investigate the effect of health insurance on primary and secondary outcomes, the analysis will use an intention-to-treat (ITT) approach where participants will be analysed in their allocated randomised study group. If there are non-compliers, i.e., participants and economic dependents who do not use the health insurance product when sick, we will also estimate the local average treatment effect (LATE). To investigate the effect of health insurance on primary and secondary outcomes, baseline characteristics will be compared for the treatment and control groups and determine whether there is differential attrition between the two groups. Outcomes for the treatment versus the control group will then be compared accounting for any baseline or attrition differences using ordinary least squared. The analysis will be conducted for all women and then separately for women engaging in transactional and commercial sex separately. A causal mediation analysis will be conducted to assess how much of the effect of health insurance on STI and HIV acquisition operates through risky sexual behaviours.

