**Eligibility criteria {10}**

Eligibility inclusion criteria for participation are:

1. Be engaged in commercial or transactional sex in Yaoundé, Cameroon
2. In receipt of a recruitment coupon (given by RDS)
3. Aged over the age of 15
4. Not married
5. Identify as woman
6. Have at least one economic dependent living in Yaoundé
7. Have their own, password protected, phone and be able to respond to SMS messages
8. Be HIV negative at enrolment

Eligibility exclusion criteria for participation are:

1. Those under 21 years old who cannot obtain parenteral or guardian consent to participate in the study

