**Sample size {14}**

The baseline study has recruited 1,508 unmarried girls and young women engaging in transactional (753) and commercial (755) sex in Yaoundé, Cameroon. Currently, 1,147 participants have been randomised via participatory randomisation, 568 participants allocated to the control arm and 579 allocated to the treatment arm. To maximise statistical power, STI-positive participants receive free treatment at baseline to start the trial with an STI-free cohort. Participants will also receive free treatment at midline to allow for the possibility to observe more than one STI per participant over the trial period. Free treatment will also be provided at endline for ethical reasons. Assuming that 20% of participants will get at least one STI over the trial period, this sample size is sufficient to show a decrease of 30% (6 percentage points) in the incidence of any STI in the treatment group assuming 80% power and a significance level of 5%. To conduct analysis separately among the sub-samples of those engaging in commercial and transactional sex, the MDE is a ~40% reduction (8.3 percentage points) in STI incidence. Assuming an HIV incidence of 4% over the trial period, the sample size would allow the detection of a decrease of 65% in HIV incidence (2.6 percentage points).

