**Assignment of interventions: allocation**

**Sequence generation {16a}**

Randomisation is conducted at the individual level using a participatory approach with a target of a 1:1 ratio to treatment or control group stratified by engagement in commercial or transactional sex. Formative research, conducted before randomisation, found that participatory randomisation was the preferred method of randomisation by the target population. Participatory randomisation was deemed fairer and more transparent than computer-based randomisation.

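### The primary OLS adjusts for whichever baseline or attrition differences are observed, so the all-women model is settled after the data are seen and is not tied to the stratifier or the baseline STI result

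*Protocol*

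**What the plan says.** Protocol, Statistical methods for primary and secondary outcomes {20a}, sets an order of work. First, "baseline characteristics will be compared for the treatment and control groups and determine whether there is differential attrition between the two groups". Outcomes are then "compared accounting for any baseline or attrition differences using ordinary least squared". The section names no covariate and no threshold for what counts as a difference. It does not say how an attrition difference would enter a regression.

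Two variables known before allocation are natural candidates for the model:

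- **Stratum.** Under Sequence generation {16a} allocation is "stratified by engagement in commercial or transactional sex". In {20a} this factor appears only through separate analyses: "The analysis will be conducted for all women and then separately for women engaging in transactional and commercial sex separately". It is not named as a term in the all-women model.
- **Baseline STI result.** Under Plans for assessment and collection of outcomes {18a}, "At baseline, we will test for syphilis, chlamydia, gonorrhoea and trichomoniasis". The section on non-adherence and missing data {20c} uses baseline infection only to remove some women in a further analysis.

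Baseline HIV cannot serve as a covariate, because an inclusion criterion is "Be HIV negative at enrolment".

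**The concern.** A covariate helps a randomised comparison when it predicts the outcome. Whether it happens to differ between arms is a poor guide to that. A rule driven by observed differences lets in irrelevant variables that differ by chance, and can leave out prognostic ones that look balanced.

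Because neither the candidate variables nor the threshold is stated, two competent analysts could follow the same sentence and report different primary estimates. At stake are the definition of the primary estimate and some precision.

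The sentence also puts attrition differences under the same regression. Covariates in OLS can deal with loss explained by those covariates, but not with loss that depends on the outcome itself.

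**Working it through.** **Inputs.** Sample size {14} gives a control risk of 20% ("Assuming that 20% of participants will get at least one STI over the trial period"), a reduction of 6 points (to 14%), 80% power, 5% significance, and 568 control and 579 treatment women randomised. A two-sided test is assumed. The share of outcome variance explained by the covariates, R², is not given and is varied below.

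**1. The plan's own figure.** The pooled risk is (568×0.20 + 579×0.14)/1,147 = 0.1697.

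- Null SE = √[0.1697×0.8303×(1/568 + 1/579)] = 0.02217
- Alternative SE = √(0.20×0.80/568 + 0.14×0.86/579) = 0.02213
- Power = Φ[(0.06 − 1.96×0.02217)/0.02213] = Φ(0.748) = 77.3%

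The stated 80% needs 615 per arm (1,230). If the 1,508 recruited had all been randomised, power would be 87.4%. At 1,147 the detectable difference is 6.2 points, which rounds to the stated 6. The stated figures fit an unadjusted comparison and claim no gain from covariates.

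**2. A fixed model.** Adjustment multiplies the residual variance by (1 − R²), so power = Φ[0.06/(0.02213×√(1 − R²)) − 1.96]. This uses the alternative SE throughout, so it starts at 77.4% instead of 77.3%.

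| Assumed R² | Power |
|---|---|
| 0 | 77.4% |
| 1% | 77.8% |
| 2% | 78.2% |
| 5% | 79.4% |
| 10% | 81.5% |

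For scale, with equal strata and 20% overall risk, a risk gap d between strata gives R² = (d²/4)/0.16. A gap of 10 points gives 1.6%, and 18 points gives 5.1%. If 20% of women are STI-positive at baseline (assumed), a gap of 25 points between baseline positives and negatives gives R² = 0.16×0.25²/0.16 = 6.3%.

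**3. Fixed model against the imbalance rule.** This is a simulation with 10,000 data sets per setting, 1,147 women, a 30% relative reduction from 20%, and robust standard errors. There are ten baseline covariates: stratum, baseline STI and eight unrelated to outcome. The imbalance rule adjusts for any covariate that differs between arms at p<0.05. The risk gaps for stratum and baseline STI are 5 and 12.5 points (R² about 2%) or 10 and 25 points (R² about 8%).

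| | R² about 2% | R² about 8% |
|---|---|---|
| Power, fixed model | 78.7% | 79.5% |
| Power, imbalance rule | 77.9% | 76.7% |
| Type I error, fixed model | 4.7% | 4.9% |
| Type I error, imbalance rule | 4.7% | 4.6% |
| Type I error, most favourable of six covariate sets | 6.0% | 6.9% |

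The gain in power is 78.7 − 77.9 = 0.8 points and 79.5 − 76.7 = 2.8 points. The last row is a worst case of free choice, not a description of the plan.

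**4. How often the rule would be triggered.** Under sound randomisation, k independent characteristics tested at 5% give at least one difference with probability 1 − 0.95^k: 23% for 5, 40% for 10 and 64% for 20.

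**The case against.** **Covariate lists belong in the SAP.** That is usually so, and the absence of a list would be no finding. Here, though, the protocol states a selection rule, and an SAP could fix the model only by replacing it.

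**The text does not say that covariates enter only when a difference is found.** This is correct. A reader might infer that the stratum and baseline STI result are excluded. The wording does not support that; it leaves the model untied to them.

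**Differences need not be chance.** This stands in part. Treatment-arm women re-consent after the draw and leave if they decline (Implementation {16c}), and data already collected from withdrawn women are removed (Participant withdrawal). Baseline differences in the analysed set can therefore be systematic, so looking for them has a purpose. It is a reason for a separate attrition analysis, not for choosing the primary model by imbalance.

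**Analysts are blinded ({17a}).** This limits steering towards a favourable result. It does not define the model, and other researchers are unblinded.

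**The gain may be very small.** This also stands. Baseline positives are treated ("STI-positive participants receive free treatment at baseline to start the trial with an STI-free cohort"), which may weaken the baseline result as a predictor. At R² of 1% to 2% the analytic gain is under one point.

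**Inverse-probability weighting is no stronger remedy.** It relies on measured baseline variables, as the OLS does. Only bounds address loss that depends on outcome, and Lee bounds carry their own monotonicity assumption.

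**Conclusion.** The concern holds in a limited form. The protocol's stated rule makes the primary adjustment set depend on observed differences, and the all-women model is not tied to the stratifier or the baseline STI result. The main cost is an under-defined primary estimate. The secondary cost is about 1 to 3 points of power, resting on an assumed R² of roughly 2% to 8% and the other simulation settings above.

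Three stronger readings are not supported:

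- **Inflated false-positive rate.** Applied mechanically, the rule keeps type I error near 5%. The 6.0% to 6.9% figures require picking the most favourable of six models, which the protocol does not propose.
- **A claim that outcome-dependent loss is solved.** The protocol does not say this. The narrower point is that OLS covariates should not be relied on for it.
- **An underpowered trial because of this rule.** The gap between 77.3% and 80% comes from the number randomised and is a separate matter.

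**What to change.** Before the final analysis, and whatever the baseline table shows:

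1. Fix the all-women primary model as OLS of outcome on arm and commercial/transactional stratum, with heteroskedasticity-robust standard errors. For the STI outcome, add the baseline result for the same STIs that make up that outcome. This has to be spelled out: the primary outcome lists three STIs, four are tested at baseline and endline, and two at midline. The HIV model has no baseline-result term, because baseline HIV is constant.
2. Keep adjustment for observed imbalances as a labelled sensitivity analysis.
3. Report attrition by arm against the numbers randomised, and add bounds, such as Lee bounds, as a sensitivity analysis. Inverse-probability weighting is optional; state that it corrects only loss explained by measured baseline variables.
4. Add CBO site only if it is defined and shown to be separable from sex-work type.

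The cost is a short change of wording and a few lines of Stata. The stratum and baseline STI results are already collected. The Trial status section says women are still being followed up, so the final model can still be set in advance; record the date of the decision relative to the midline interim analysis.

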**Trial design {8}**

This study is a stratified cluster randomised controlled superiority trial with two groups: control and treatment. Private participatory randomisation will be conducted with a target of a 1:1 allocation stratified by the type of risky activity, commercial sex or transactional sex.

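### The insurance effect is estimated separately in the transactional and commercial sex groups, with no stated estimate or test of the difference between the two effects

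*Protocol*

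**What the plan says.** Statistical methods {20a} plans an intention-to-treat comparison by ordinary least squares (OLS), adjusted for baseline or attrition differences. On the two groups it says: "The analysis will be conducted for all women and then separately for women engaging in transactional and commercial sex separately". The pooled analysis therefore comes first, followed by one model per group. No arm-by-stratum term is named, and no direct comparison of the two effects.

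The heterogeneity analyses under Methods for additional analyses {20b} ask whether the effect of economic shocks varies. They do not ask whether the effect of insurance differs by type of sex work.

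The factor is built into the design. Trial design {8} has allocation "stratified by the type of risky activity, commercial sex or transactional sex". Sample size {14} treats the full sample as "sufficient to show a decrease of 30% (6 percentage points) in the incidence of any STI in the treatment group", and for the separate analyses states that "the MDE is a ~40% reduction (8.3 percentage points) in STI incidence".

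**The concern.** Two separate models give two estimates and two p-values. A reader who wants to know whether insurance works in both groups will naturally set the p-values side by side. When each group has only moderate power, one significant and one non-significant result is common even if the true effects are the same. That pattern says little about whether the effects differ.

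The groups are two distinct populations for policy. At stake is a mistaken conclusion that insurance helps one of them and not the other.

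**Working it through.** **Inputs**
- Sample size {14}: "Assuming that 20% of participants will get at least one STI over the trial period". I read the 20% as the control-arm risk.
- Overall effect: 6 points (20% vs 14%). Group effect: 8.3 points (20% vs 11.7%). Power 80%, significance level 5%; sidedness is not stated, so two-sided is assumed.
- Randomised: 568 + 579 = 1,147. The baseline groups are 753 and 755. The split of the 1,147 by group is not given; an even split gives 1,147/4 = 286.75, about 287 per arm per group.
- Women are treated as independent, with no loss after randomisation except in step 5.

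**Formula.** With n per arm, risks a and b, and m = (a + b)/2:

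power = Φ{[|a − b| − 1.96·√(2m(1 − m)/n)] / √([a(1 − a) + b(1 − b)]/n)}

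**1. The protocol's own figures**
- Overall, n = 573.5, 20% vs 14%: (0.06 − 1.96 × 0.02218)/0.02211 = 0.747, so power is 77.3%. The effect detectable at 80% power is 6.2 points; 80% power for 6 points needs 615 per arm, 1,230 in all.
- Per group, n = 287, 20% vs 11.7%: (0.083 − 1.96 × 0.03049)/0.03029 = 0.767, so power is about 78%. The detectable effect is 8.5 points.

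Both stated figures are near misses; they fit a total of about 1,206 to 1,230. The gap does not affect what follows.

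**2. Power per group if the 6-point effect holds in both**

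(0.06 − 1.96 × 0.03136)/0.03126 = −0.047, so power is 48.1%.

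**3. Patterns of significance with identical 6-point effects.** The groups contain different women, so the two tests are independent:
- exactly one significant: 2 × 0.481 × 0.519 = 0.499
- both: 0.481² = 0.231
- neither: 0.519² = 0.269

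A simulation of 400,000 trials with 287 per arm per group gave 48.5% power and 49.8% with exactly one significant.

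**4. The same at the protocol's 8.3 points in both groups** (power 0.779)
- exactly one significant: 2 × 0.779 × 0.221 = 0.344
- both: 0.779² = 0.607
- neither: 0.221² = 0.049

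**5. Sensitivity of step 3**
- Follow-up loss of 0 to 23% (the upper end borrowed from the pre-randomisation attrition given in the Discussion): power per group 48.1% down to 38.9%; exactly one significant in 49.9% down to 47.5%.
- A 40:60 split of the groups: power 40.1% and 55.4%; exactly one significant in 51%.

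**6. The interaction test**
- SE of one group's effect: √[(0.16 + 0.1204)/287] = 0.0313. SE of the difference between effects: √2 × 0.0313 = 0.0442, or 4.4 points.
- 95% CI half-width: 1.96 × 4.42 = 8.7 points.
- Difference detectable at 80% power: 2.80 × 4.42 = 12.4 points.
- Power for a true 6-point difference: Φ(0.06/0.0442 − 1.96) = 27%.
- In the simulation with identical 6-point effects, it declared a difference in 5.1% of trials.

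**The case against.** The strongest case against is that nothing in the protocol is false. The group analyses are prespecified, match the randomisation strata, and come with an openly stated, larger detectable effect. The research hypothesis and objectives treat the two groups together and pose no question about a difference. Separate OLS fits also lose no information: the difference and its interval can be computed from the two estimates and standard errors. An interaction term may sit in a statistical analysis plan that is not shown. And the remedy has low power.

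Most of this stands and limits the point. Three stronger readings that a reader might infer are not supported:
- *That the groups are analysed only in separate models.* The same sentence puts the analysis of all women first.
- *That a one-group-only result is the most likely outcome under the plan's assumptions.* This is so at 6 points in both groups. At the 8.3 points stated for these analyses, both groups significant is the most likely pattern (about 61%).
- *That the investigators will conclude from contrasting p-values.* No section says so.

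What remains is that the protocol does fix how the groups will be analysed, and the stated method delivers no estimate of the difference unless someone adds it. The 8.3 points is a detectable effect, not a forecast. With near-equal groups, 8.3 points in both would also imply about 8.3 overall, more than the 6 points used for the full sample. The 6-point scenario is therefore a fair one to examine.

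**Conclusion.** The point holds as a minor improvement to the analysis. With separate models and no stated comparison of effects, exactly one group would be significant in about 50% of trials with identical 6-point effects, and in about 34% with identical 8.3-point effects. These are chances of a misleading pattern; it becomes an error only if the pattern is read as a difference. Under identical 6-point effects, requiring the interaction test before claiming a difference cuts that risk to about 5%.

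The figures assume an even split of the 1,147 by group, a 20% control risk, two-sided 5% tests and independent women. They change little with follow-up loss up to 23% or a 40:60 split. The pooled conclusion is unaffected.

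**What to change.** Keep the pooled analysis and both group estimates. Obtain the group effects, with confidence intervals, from one OLS model with arm, stratum and arm-by-stratum terms. If the estimates are to match those from separate models exactly, interact the adjustment covariates with stratum as well. Report the difference between the two effects in percentage points with its 95% CI, and state in advance that the effects will be said to differ between groups only on that interaction.

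The cost is one model term (plus covariate interactions if wanted) and one sentence. Trial status records that participants were still in follow-up at this protocol version, so the rule could be set before the endline analysis. The limitation should be stated with it: at about 12.4 points detectable with 80% power, a non-significant interaction does not show that the effects are equal.
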